**Methods:**

A mixed method evaluation strategy has been launched involving: i) baseline and endline randomized sample surveys with 247 clusters dispersed in 14 districts of the Northern and Volta Regions to assess the difference in difference effect of stepped wedge differential cluster exposure to CHPS+ activities on childhood survival, ii) a monitoring system to assess the association of changes in service system readiness with CHPS+ interventions, and iii) a program of qualitative systems appraisal to gauge stakeholder perceptions of systems problems, reactions to interventions, and perceptions of change. Integrated survey and monitoring data will permit multi-level longitudinal models of impact; longitudinal QSA data will provide data on the implementation process.

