### Impact research: The household survey

Using questionnaires that are designed to replicate the national 2014 Demographic Health Health Survey, CHPS+ will conduct baseline and endline demographic surveys for assessing impact. The baseline CHPS+ project survey sample is designed to obtain information to detect a 15% reduction in under-five mortality with 80% power at 5% level of significance in each of the two study regions. Overall, the interventions are taking place in eight districts (four in each region) while another eight districts (four in each region) are being used as comparison districts. Survey sampling is designed to draw a representative sample of the number of women of reproductive age (15–49 years) in three of the four treatment districts in each region and in four randomly selected comparison districts. Thus, a total of fourteen districts, seven per region, were included in the baseline survey. A two-stage stratified cluster sampling approach was used. In the first-stage, census enumeration area clusters were sampled, and in the second-stage, households will be sampled from the first-stage clusters. Because a minimum of 30 clusters is conventional for the first stage of cluster sampled household surveys [41], a relatively conservative starting point of 40 clusters each for intervention and control districts in each region was selected.

Because the sample is designed to detect separate under-five mortality effects in each of two regions, sample size calculations were completed independently for each region. Final sample size and sampling parameters were based on region-specific estimates of census enumeration area intra-cluster correlation (ICC) and the number of children under five expected per woman. These parameters were calculated from publicly available data from the 2014 Ghana Demographic and Health Survey [42]. In Volta Region, ICC was higher and the number of children expected per woman was lower than in Northern Region. Therefore, a larger number of clusters and a larger number of households per cluster will be sampled in Volta Region. Sampling requirements for each region were calculated using a software system for conducting power calculations in multi-level randomized experiments known as Optimal Design [43].

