#### Sample design

The sampling frame for the first stage was from the 2010 Population and Housing Census which provided a complete listing of Enumeration areas in the fourteen districts to be surveyed. The sampling frame contained information such as the location and estimated number of households. In each region, Enumeration areas were stratified by rural versus urban and by the estimated number of households in the cluster. Clusters were stratified into three groups (small, medium, or large yielding a total of 6 strata in each district. Enumeration areas were sampled from each stratum using probability proportional to population size (PPS). Weights will be applied at the cluster level to standardize probabilities of household selection based on the relative population size of clusters.

To obtain a sampling frame for the second-stage sampling, a household listing of all households in each cluster was compiled based on census information on household size and number women of reproductive age (15–49) in each household. Households were then stratified into three strata defined by the number of eligible women in each household.

To maximize sample efficiency for difference-in-difference estimation at the endline, baseline sample clusters will be reused without modification to permit longitudinal observation of clusters and the assessment of the average treatment effect arising from the timing of exposure of clusters to project interventions. The second-stage sampling procedure will be repeated, yielding a household sample for the longitudinal observation of children exposed versus unexposed to interventions over the duration of the project, with provision for statistical adjustment of baseline and endline differentials and changes in project endpoints that are unrelated to CHPS+ interventions.

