#### Assessing impact

CHPS+ will have core, intermediate outcome, and process endpoints, each requiring systems of data capture, data management, and analysis to gauge project impact. These core endpoints and indicators will be consistent with the Ghana Ministry of Health core indicators of health improvement with instruments designed to maximize comparability with national Ghana Demographic and Health Survey instruments. This will involve indicators of under-five mortality, infant mortality, and neonatal mortality by gender of child; age specific and total fertility rates and proximate determinants that are relevant to policy; and indicators of parental health seeking behavior, such as skilled attendant delivery, care of sick children, exposure to community-based services, distance to health facility and utilization of facilities for essential care. Critical covariates essential to the understanding of equity and impact, such as educational attainment, household economic status, and distance to service point will also be assessed.

CHPS+ will utilize impact assessment strategies that have worked well for GEHIP. Routine compilation of time trends indicators will be supplemented with end-of-project *difference-in-differences* calculations for each indicator. This econometric strategy has been applied elsewhere for the assessment of non-randomized plausibility trials [44–46] and successfully applied to the evaluation of GEHIP [47]. The procedures involve collecting data in baseline clusters, monitoring systems changes and the timing of these changes, and repeating the survey in baseline clusters with a separate endline stage two sample to gauge effects. Regression analysis is based on merged baseline and endline data for the estimation of parameters that control for baseline differences and contextual confounders, changes over time that are unrelated to interventions, and conditional effects of interventions that control for these confounding changes by estimating net intervention effects. A difference-in-difference estimate of program effects is given by the child survival effect of CHPS+ systems interventions (**S**) where individual child i is scored 1 if the household is located in a cluster that is exposed to CHPS treatment and zero otherwise and z is scored 1 if the case *i* is observed in the endline and zero if the case is observed in the baseline. If all covariates are equal to zero for child *i*, (*i.e.,*
*X*_*1*_*=**0*, *X*_*2*_*=**0,...*

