*X*_*k*_*=**0,*
*S=0,*
*Z=0*), the underlying mortality hazard is *h*_0_(t) and the conditional multilevel proportional hazard model is:1$$ {\boldsymbol{h}}_{x\sim SZ}\left(\boldsymbol{t}\right)={\boldsymbol{h}}_{\mathbf{0}}\left(\boldsymbol{t}\right){\boldsymbol{e}}^{\left[{\beta}_0+\sum \limits_{k=1}^K{\beta}_k{X}_{ij k}+\gamma {S}_j+\delta {Z}_{ij}+\zeta {S}_j{Z}_{ij}+{\mu}_j+{\varepsilon}_{ij}\right]} $$for all *t*, where:

*X̃*_*i*__*j*__*k*_ represents *K* characteristics of child *i* in cluster *j*;

*S*_*j*_ indicates whether cluster *j* is in the treatment area (*S* = 1) or comparison area (*S* = 0);

*Z*_*ij*_ indicates whether the person time of child *i* in cluster *j* occurs during the post-treatment period (*Z* = 1) or pre-treatment period (*Z* = 0);

*S*_*j*_*Z*_*ij*_ is a cross-level interaction term of treatment and period for estimating the net effect of treatment in the difference-in-differences approach;

and

*μ*, *ε* represent residuals for cluster and individual levels, respectively.

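### Equation 1 gives each re-surveyed cluster one time-constant residual, so a model-based standard error for the mortality effect would largely ignore clustering and be too small if clusters change differently between periods

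*Protocol article*

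**What the plan says.** All references are to the protocol article.

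- **Design.** Sample design states that "baseline sample clusters will be reused without modification to permit longitudinal observation of clusters". Assessing impact describes "repeating the survey in baseline clusters with a separate endline stage two sample to gauge effects". The survey data are thus repeated cross-sections of households within a fixed set of clusters.
- **Model.** Equation 1 in Assessing impact is a multilevel proportional hazards model with covariates, treatment area S_j, period Z_ij and their product. The coefficient zeta on S_j × Z_ij carries the effect; this product "is a cross-level interaction term of treatment and period for estimating the net effect of treatment in the difference-in-differences approach". The random part is mu_j, indexed by cluster only, and epsilon_ij, indexed by child; these "represent residuals for cluster and individual levels, respectively". The equation has no cluster-by-period term, random slope on Z, or district term. No robust variance is described.
- **Size.** The abstract gives "247 clusters dispersed in 14 districts of the Northern and Volta Regions". The household survey section aims to "detect a 15% reduction in under-five mortality with 80% power at 5% level of significance in each of the two study regions". It says the sample was sized using region-specific enumeration-area ICCs, but prints no ICC value.
- **Delivery.** The section on systems learning districts makes the district management system the focus of intervention. Seven districts per region are surveyed: three treatment and four comparison.

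**The concern.** S varies between clusters and Z varies within them. A cluster effect that is identical in both periods is subtracted out when each cluster's change is formed, so mu_j adds almost nothing to the variance of zeta. This is right only if children in the same cluster are as alike across periods as within one, that is, if the cluster autocorrelation is 1.

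The article's own account points the other way. The project lasts five years, exposure is phased and recorded by cluster, and implementation is meant to spread outward from demonstration zones. Local changes of this kind are shared by a cluster's children in one period. The common period effect delta cannot absorb them, because it is the same for all clusters, and epsilon_ij cannot, because it belongs to single children. Equation 1 has nowhere else to put them.

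At stake is the standard error of the coefficient that tests the impact hypothesis. The clustering used to size the survey would largely disappear from that test.

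**Working it through.** **1. Can the plan's 80% power be reproduced?** No. Baseline mortality, ICC, children per cluster and the split of the 247 clusters by region and arm are not given. The only split mentioned is "a relatively conservative starting point of 40 clusters each for intervention and control districts in each region was selected". The claim is neither confirmed nor refuted here.

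**2. Cancellation (linear approximation, equal exposure in both periods).** With m children per cluster-period, the change in cluster j is

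ȳ_j1 − ȳ_j0 = delta + zeta·S_j + (ε̄_j1 − ε̄_j0).

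mu_j has gone, leaving variance 2σ_e²/m per cluster. If a cluster-by-period effect with variance σ_ν² exists, the variance is 2(σ_e²/m + σ_ν²). Write σ_e² = 1 − ICC and σ_ν² = ICC(1 − r), where r is the cluster autocorrelation. The true variance then exceeds the reported one by about

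R = 1 + m·ICC·(1 − r)/(1 − ICC),

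and the two-sided false-positive rate at nominal 5% is 2[1 − Φ(1.96/√R)].

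**3. Simulation of Equation 1's cluster intercept.** The assumptions, none from the article, are 123 clusters per region, seven districts (3 v 4), 8% mortality, total cluster log-hazard SD about 0.4, no treatment effect and 2,000 runs per setting.

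| Share of cluster variance specific to period | m | Reported SE of zeta | SE ignoring clustering | True SD of zeta | False-positive rate |
|---|---|---|---|---|---|
| 0% | 40 | 0.1384 | 0.1384 | 0.1380 | 4.6% |
| 0% | 80 | 0.0977 | 0.0977 | 0.0951 | 4.2% |
| 20% | 40 | 0.1385 | 0.1385 | 0.1512 | 6.8% |
| 20% | 80 | 0.0977 | 0.0977 | 0.1127 | 8.8% |
| 50% | 40 | 0.1386 | 0.1386 | 0.1584 | 8.9% |
| 50% | 80 | 0.0979 | 0.0979 | 0.1228 | 11.8% |

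The reported SE equals the independence SE to four decimals throughout. In a companion simulation (4,000 runs per setting), a cluster-level robust variance gave 4.4 to 5.1% in all of these settings.

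**4. Values roughly compatible with the power claim.** Assume an even split, so k = 247/4 = 61.75 clusters per arm per region, a two-sided test, and a standard two-arm cluster comparison. With q = 0.85p, children per arm before clustering are

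n = (1.96 + 0.84)²[p(1 − p) + q(1 − q)]/(p − q)².

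With unrounded normal quantiles this is 10,155 at assumed under-five mortality of 6%, 7,466 at 8% and 4,777 at 12%. Effective n per arm cannot exceed k/ICC, so the claim requires ICC below 61.75/10,155 = 0.0061 (6%) to 61.75/4,777 = 0.0129 (12%). Solving k·m = n[1 + (m − 1)ICC] gives m = n(1 − ICC)/(k − n·ICC).

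| ICC | Mortality | m | Rate at r = 0.8 | Rate at r = 0.5 |
|---|---|---|---|---|
| 0.002 | 12% | 91 | 5.4% | 6.1% |
| 0.002 | 6% | 245 | 6.1% | 7.9% |
| 0.005 | 12% | 125 | 6.5% | 8.7% |
| 0.005 | 8% | 304 | 8.6% | 14.0% |

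Example, last row: m = 7,466 × 0.995/(61.75 − 37.33) = 304. At r = 0.5, R = 1 + 304 × 0.005 × 0.5/0.995 = 1.76, and 1.96/√1.76 = 1.48, giving 14%. ICC 0.005 with 6% mortality is left out. It is close to the ceiling and would need m = 10,155 × 0.995/(61.75 − 50.78), about 920 children per cluster.

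**5. One level up.** Adding a district-by-period SD of 0.10 to the 20% setting gives these false-positive rates at m = 40 and 80:

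- Equation 1: 14.0% and 20.6%
- cluster-level robust variance: 11.1% and 14.3%
- t-test on district log-rate changes: 4.8% and 4.3%

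**The case against.** **The variance estimator is not fixed.** Equation 1 is one display in a condensed article, and a robust or design-based variance is compatible with it. An analysis plan that is not shown may specify one. This stands, and it makes the point conditional: a reader might infer that the p-value and interval are certainly too favourable, but the article does not settle how the standard error is obtained. It does not remove the point. The article commits to a specific random structure that fits its own sampling design badly. The cluster weights in Sample design deal with selection probabilities, not with change over time.

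**Large error rates are not supported.** A reader might take an ICC of 0.02 to 0.05 with about 100 children per cluster and arrive at 10 to 30%. Those values cannot be reconciled with the stated power under a standard two-arm cluster calculation, whose ceiling is about 0.006 to 0.013. They should not be used. The simulation in step 3 is not calibrated to the power claim either. At 8% mortality, an SD of 0.4 corresponds to an ICC of about 0.08(e^0.16 − 1)/0.92 = 0.015, above the ceiling of 61.75/7,466 = 0.008. Its error rates are illustrative.

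**The period is defined in two ways.** The text before Equation 1 scores Z by survey; the definitions below it score Z by when the child's person time falls. On the second definition pre- and post-treatment exposure may adjoin, so autocorrelation could be higher than for two surveys years apart. This stands as a reason for caution about r = 0.5. The cancellation of mu_j is unaffected, apart from being exact only when exposure is balanced.

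**District-level inference would absorb much of this.** This is largely true, and the fix includes it.

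**Conclusion.** The structural point holds: with the same clusters in both periods and one time-constant residual, a model-based standard error for zeta is close to the independence standard error. Harm requires two further conditions, neither fixed by the article: model-based standard errors are used, and clusters change differently between periods. The second is likely over a five-year phased roll-out. Without such change the test is valid.

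The size is uncertain. The false-positive rate is about 5.4 to 14% for ICC 0.002 to 0.005 with 50 to 80% of cluster variance persistent, and about 7 to 12% in the simulation. Either range could move with the missing inputs, and change shared within districts would add to it. The documents do not support the further inference that the 80% power is wrong. This is a change that should be made; it does not show that the trial's conclusion would fail.

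**What to change.** 1. In Equation 1, replace mu_j with mu_j + nu_jz, where nu_jz is a cluster-by-period random effect (a random cluster slope on Z is an alternative). Base the test and interval of zeta on that model.
2. Do the same in the difference-in-differences calculations for the other survey indicators.
3. Also allow for district-by-period variation, for example by a district-level analysis or a variance grouped by district with a small-sample correction, given only seven surveyed districts per region. A cluster-by-period term or a cluster-level robust variance alone does not protect against shocks shared by a district.
4. Use one definition of Z, so that the period in the random effect matches the period in the contrast.

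No new data are needed. The cost is a wider interval for zeta where clusters or districts drift, and district-level inference will have few degrees of freedom.

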### Systems learning districts (SLD)

CHPS+ is grounded in experience with planned organizational change in Ghana. Taken as a set of activities, Fig. 2 portrays a model for catalyzing implementation-based learning and “guided diffusion” for spreading commitment to community-engaged CHPS implementation and functioning [18–20]. The district management system is the focus of intervention, with district team stakeholders constituting players in the process of instituting large-scale change. To implement the CHPS+ program, key elements of the GEHIP approach will be transferred to regional, district, sub-district, and community-level teams through exchanges that are field based and designed to demonstrate core GEHIP action agenda. Since all district implementers cannot possibly be included in a program of exchange, a program of interchange and outreach is envisioned that will focus on catalytic leadership implementation units that represent the authority and implementation hierarchy in participating districts [21].

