## Methods/design

### Hypotheses and goals

CHPS+ will test the primary implementation hypothesis that the pace of expansion of CHPS population coverage can be significantly increased relative to the pace of CHPS expansion in districts not yet exposed to CHPS+ interventions. Research is also designed to test the impact hypothesis that CHPS+ implementation will improve infant and child survival. A three component mixed method evaluation strategy has been launched for program evaluation involving: i) baseline and endline randomized cluster sample survey research with 247 census enumeration clusters dispersed in 14 districts of the Northern and Volta Regions for assessing the effect of cluster exposure to CHPS+ activities on childhood survival; ii) a service delivery point monitoring system for assessing the association of changes in service system readiness with CHPS+ interventions; and iii) a program of qualitative systems appraisal (QSA) to gauge stakeholder perceptions of systems problems, reactions to CHPS+ interventions, and perceptions of change. Temporal variance in project implementation will be monitored to provide stepped wedge recorded differential exposure to operations. Integrated survey and M&E data will permit multi-level longitudinal models of impact; longitudinal QSA data will provide data on the implementation process.

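### Equation 1 carries residuals for enumeration area and child only, although CHPS+ is delivered to districts, so the standard error of the mortality effect is too small whenever district trends differ

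*Protocol article*

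**What the plan says.** **Level of the intervention.** The Protocol article (Systems learning districts) says that "The district management system is the focus of intervention". Under Impact research: The household survey, "the interventions are taking place in eight districts (four in each region) while another eight districts" serve for comparison. The survey covers "three of the four treatment districts in each region and in four randomly selected comparison districts", and "a total of fourteen districts, seven per region, were included in the baseline survey".

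**Sampling units.** Hypotheses and goals gives "247 census enumeration clusters dispersed in 14 districts of the Northern and Volta Regions". The household-survey section makes these the first-stage units: "In the first-stage, census enumeration area clusters were sampled". The same section bases the sample size on the intra-cluster correlation of enumeration areas, and claims 80% power at the 5% level for a 15% reduction in under-five mortality in each region separately.

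**Model.** In Assessing impact, Equation 1 is a proportional hazards model. S_j states whether cluster j lies in the treatment or the comparison area, Z_ij marks the period, and zeta, the coefficient of their product, is the net programme effect. The remaining random terms "represent residuals for cluster and individual levels, respectively".

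The article prints no district term, district-by-period term, district-clustered variance or allowance for a small number of districts.

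**The concern.** As printed, S_j takes one value for every enumeration area in a district, so treatment status varies over 14 districts and not over 247 clusters. The same enumeration areas are surveyed at both rounds, so level differences between clusters, or between districts, that stay constant over time largely cancel in the treatment-by-period contrast. What does not cancel is a change in mortality peculiar to one district, for example through staffing or an outbreak. All of that district's roughly 18 enumeration areas share the change (247 / 14 = 17.6), and Equation 1 has nowhere to put it.

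Zeta is the answer to the child-survival hypothesis. If ordinary differences between district trends are read as sampling noise among many independent clusters, the interval is too narrow and the risk of a false claim of lives saved exceeds the nominal level.

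**Working it through.** **The plan's own figures.** The district count reproduces: 2 x (3 + 4) = 14, that is 6 treated and 8 comparison. The 247 clusters and the 80% power cannot be reproduced, because the intra-cluster correlation, baseline mortality, children per woman and households per cluster are not printed.

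**Standard error implied by the stated power.** I take the 15% reduction as a hazard ratio of 0.85, the 5% level as two-sided, and the stated power as applying to zeta:

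SE = |ln 0.85| / (1.960 + 0.842) = 0.1625 / 2.802 = 0.0580 per region, so SE^2 = 0.003365.

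**Adding district trends.** Let tau be the standard deviation, over districts, of the true change in log mortality between rounds. Tau is an assumption; the documents give no value. Then

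Var(zeta) = SE^2 + tau^2 x (1/3 + 1/4) = 0.003365 + 0.5833 x tau^2.

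A test that reports only the first term has true two-sided error 2 x [1 - Phi(1.960 x SE / SE_true)]. The last column is the power of a district-level t-test for a 15% reduction (7 - 2 = 5 degrees of freedom, critical value 2.571).

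| tau | SE_true | SE_true / SE | True error, nominal 5% | District-level power, per region |
|---|---|---|---|---|
| 0 | 0.0580 | 1.00 | 5.0% | 61% |
| 0.02 | 0.0600 | 1.03 | 5.8% | 59% |
| 0.05 | 0.0695 | 1.20 | 10.2% | 47% |
| 0.10 | 0.0959 | 1.65 | 23.6% | 28% |
| 0.20 | 0.1634 | 2.82 | 48.7% | 13% |

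**Pooling the regions.** The sampling variance halves (SE = 0.0580 / sqrt 2 = 0.0410), and so does the district factor (1/6 + 1/8 = 0.2917). The error rates are therefore unchanged. District-level power on 11 degrees of freedom (critical value 2.201) is 95%, 85%, 59% and 25% at tau 0, 0.05, 0.10 and 0.20.

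**Cross-check by simulation under no effect.** The set-up was 6 against 8 districts, 18 clusters each and cluster standard deviation 0.3. Under-five mortality of 60 to 100 per 1000 and 30 to 100 children per cluster and round were further assumptions. A test without a district term rejected in about 5 to 7% of trials at tau 0.05, 6 to 15% at 0.10 and 13 to 36% at 0.20. It was nominal at tau 0. A district-level t-test stayed at 4 to 6%. The rates lie below the table because these scenarios have a larger sampling error than the stated power implies, so district variation is a smaller share of the total. The simulated test compared arm-by-period death totals; it did not fit Equation 1 itself.

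**The case against.** **Exposure may vary within districts.** The Abstract, Hypotheses and goals, and Sample design speak of stepped-wedge or timing-based exposure of clusters. The text leading into Equation 1 scores a child by whether the cluster is exposed. If S followed the start date in each cluster, part of the contrast would lie within districts, and counting only 14 units would be too severe. This stands as an inconsistency in how exposure is defined. It does not rescue the printed model, which defines S_j by area and contains no timing variable.

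**The variance method is not stated.** The article gives no standard-error method or reference distribution for zeta, and a district-robust variance or bootstrap could be attached to the same estimator. That is fair, and it makes the point conditional on inference that uses the printed levels. It is still more than detail left to an analysis plan, because the residual levels are printed and omit the level of delivery.

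**Covariates may absorb the differences.** The text promises control for contextual confounders and unrelated change over time. In the equation, X holds characteristics of the child and Z carries one common period effect. Neither removes a shock shared by one district.

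**Tau is invented.** This stands. A reader might infer that the false-positive rate is known to be well above 5%, or that district trends are the largest source of error beyond sampling. The documents support neither: they give no district-level variance, and at tau 0.02 the error is only 5.8%.

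**Mortality is not the primary hypothesis.** The primary implementation hypothesis is the pace of coverage, and the design is described as a non-randomised plausibility evaluation. That limits the weight of any one p-value. It also makes differing district trends no less plausible.

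**Conclusion.** The point holds in conditional form. Equation 1 does not match the level at which CHPS+ is delivered, and inference from its printed residual levels understates the standard error of zeta unless all districts share the same trend. The direction follows from the document; the size does not. The illustrative error rates rest on an assumed tau and on a standard error read back from the stated power. A larger sampling error lowers the inflation at the same tau. The power claim has the same gap, since it rests on the enumeration-area correlation alone. For region-specific effects only 7 districts carry the comparison, so about 61% power is what the implied standard error supports on 5 degrees of freedom, even with no variation in district trends.

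**What to change.** Add a district-by-period random effect to Equation 1, or regress the district log-rate changes on S. A district random intercept alone will not do, because it cancels in the contrast.

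Base the interval and p-value for zeta on district-level degrees of freedom: 5 within a region; pooled, 14 - 3 = 11 with an additive region term or 14 - 4 = 10 with region-by-treatment. A small-sample wild cluster bootstrap or a permutation by district is an alternative. Within one region, 3 against 4 districts allow only 35 arrangements, so a permutation p-value cannot fall below 1/35 = 0.029. Variance components will also be poorly estimated from 7 or 14 districts, which favours the simple regression of district changes.

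State whether S means treatment area or dated cluster exposure, and make the equation agree with the text.

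The cost is analysis wording and code, with no new data, since clusters were sampled by district. Intervals will be wider, and the 80% power per region should be restated over a range of tau, with the pooled figure alongside.
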